### Recruitment and Data Collection

The panel will be used for participant recruitment and data collection. Potential participants are registered users who meet the inclusion criteria. They must be aged ≥18 years, speak German, and be employed. Furthermore, the company with which they work must have at least 30 employees. Illiterate persons will be excluded. A message with the link to the study and the offer to participate will be sent to the database of potential participants until the required subsample of 150 people is reached for the first rounds. For the last round, a sample of 800 persons will be recruited.

Before the study, participants will receive written information about the procedure and any expected risks and side effects and the names of the people to contact. Informed consent will be obtained electronically in advance from the participants who agree to continue with the study.

### Data Analysis and Measures

#### Power

A sample size of 150 will be used for the iterative development of the questionnaire to check the retest reliability, internal consistency, and item analyses. This is methodologically justified as item analyses [20], internal consistency [21], and retest reliability [22] require between 100 and 200 people for a robust estimate.

For the CFA, the aim is to achieve a sample size of at least 800 following the rule of thumb by Bühner [23], with medium communalities (*h*^2^>0.50) and approximately 20 factors across all dimensions.

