**Results:**

As of February 2026, a first draft of 158 items has been developed based on dimension 1 of the SyMOA framework. The draft has undergone an expert review process with 2 experts in psychodynamics, who provided feedback on content validity and conceptual alignment. Approximately 20% of the items have been revised to improve clarity and theoretical precision. Data collection using a panel started in May 2025 and concluded in late August 2025, with iterative item analysis conducted thereafter.

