**Figure 1. F1:**
[figure not shown]
Study flow diagram. OPD: *Operationalized Psychodynamic Diagnosis*.

First, the SyMOA scale for dimension 1 will be converted into a set of items and evaluated by 2 experts (expert validity). To this end, a preliminary set of items for the dimension will be created based on the qualitative SyMOA instrument. The aim is to have at least 80 items, which will be answered on a 5-point Likert scale. The items will be presented in German and mostly formulated negatively, with 20% formulated positively. In a second step, the items will be tested using structural and item-level analyses by an online panel sample (n=150) and refined iteratively based on their psychometric performance. Data collection will be conducted via LimeSurvey (LimeSurvey GmbH), a secure web-based survey platform. The development process will be completed if no further adjustment of the items is necessary.

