As a third step, the retest reliability will be checked by sending the questionnaire to the same sample as that in the previous round (n=150) after 2 weeks. In a fourth step, a confirmatory factor analysis (CFA) will be carried out to check the fit of the theoretically assumed factor structure based on the SyMOA construct (sample of n=800). In addition, the discriminant validity of the questionnaires will be assessed. For this purpose, existing questionnaires used in clinical practice, such as the *Operationalisierte Psychodynamische Diagnostik–Strukturfragebogen* (OPD-SF) [17], will be used. To be able to assume that the surveyed constructs relate to the organization rather than the person completing the questionnaire, there should be a maximum of moderate correlations. For the evaluation of external validity, employee satisfaction (*Inventar zur Erfassung der Arbeitszufriedenheit* [18]) and work-related quality of life (World Health Organization Quality of Life Scale–Brief [19]) will also be administered in the last round. Although neither scale directly measures the assumed construct of organizational health dynamics, it can be assumed that there is a strong correlation between organizational health and the satisfaction and quality of life exhibited by employees. In addition, sociodemographic data such as age, gender, educational qualifications, professional experience, employment relationship, position or management function, sector, size of the company (eg, number of employees: 30-50 or 50-150), and size of the work area (eg, number of employees: 1-5, 5-10, or 10-20) will be evaluated in relation to the results.

For the development of the questionnaire for T1 to Tx (ie, from the start of data collection to the final item analysis round), as well as for the verification of the test-retest reliability for Tx+1 and the confirmatory sample for Tx+2, the recorded variables and their operationalization are listed in Table 2.

**Table 2. T2:** Data collection with instruments and time point of measurement.

Time point of measurement and measured variable	Operationalization
T1^a^-Tx^b^—development of questionnaire based on dimension 1	
Quality of the items of the scale	Item analysis: item difficulty, item selectivity, item variance, and distribution
Reliability of the scale	Internal consistency of the scale
Tx+1^c^—retest reliability	
Retest reliability	Agreement of the results of Tx+1 with those of Tx
Tx+2^d^—CFA^e^ and validity	

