Internal level of functioning of the organization	SyMOA-Q^f^ based on dimension 1 of the SyMOA^g^
Factorial validity of the scales	CFA
Sociodemographic data	Age, gender, educational qualifications, professional experience, employment relationship, position or management function, sector, size of the company (30-50, 50-150, 150-250, 250‐1000, or >1000), and size of work area (1-5, 5-10, 10-20, 20-50, and >50)
Discriminant validity via structural level of employees	OPD-SFK [17]^h^
Employee satisfaction as an external criterion	IAZ^i^ [18]
Work-related quality of life as an external criterion	WHOQOL-BREF [19]^j^

a T1 marks the start of data collection.

b Tx refers to the final round of phase 2 (completion of item analysis).

c Tx+1 indicates the retest reliability assessment (phase 3).

d Tx+2 refers to the confirmatory factor analysis and validity testing (phase 4).

e CFA: confirmatory factor analysis.

f SyMOA-Q: Systematic Multidimensional Organizational Assessment–Questionnaire.

g SyMOA: Systematic Multidimensional Organizational Assessment.

h OPD-SFK: *Operationalisierte Psychodynamische Diagnostik–Strukturfragebogen Kurz*.

i IAZ: Inventar zur Erfassung der Arbeitszufriedenheit.

j WHOQOL-BREF: World Health Organization Quality of Life Scale–Brief.

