### Future Directions

Future research should extend this work by developing and validating questionnaire-based measures for the remaining dimensions (2-3) of the SyMOA framework. This study focuses exclusively on the development and validation of a questionnaire based on dimension 1 of the SyMOA framework, which addresses sociotechnical integration and the internal level of organizational functioning. Accordingly, the validity evidence obtained in this study applies only to this dimension and does not yet support claims regarding the assessment of organizational dynamics in their entirety. Expanding beyond dimension 1 will enable a more comprehensive operationalization of systems psychodynamic organizational diagnostics and allow for an integrated assessment across multiple organizational domains.

A further essential step will be the normative calibration of the instrument. This study is explicitly focused on the development and initial psychometric validation of the SyMOA-Q, including the examination of factorial structure, internal consistency, and first evidence of construct validity. Establishing norms based on data from organizations across different industries, organizational sizes, and hierarchical levels is necessary to enhance the interpretation of scores. In this study, scoring is conceptualized at the level of factor scores for the subscales of dimension 1, with the option of examining higher-order factor structures in subsequent research.

In addition, multilevel research designs represent a key next step. This study is an initial step in the development and psychometric validation of the SyMOA-Q focusing on systems psychodynamic organizational dynamics as perceived by individuals. Future studies should use clustered sampling designs in which multiple respondents are nested within clearly identified organizations. This will allow for the examination of aggregation statistics (eg, intraclass correlations and within-group agreement indexes) to determine whether and under which conditions individual perceptions can be meaningfully aggregated to the organizational level. Building on these analyses, multilevel CFAs should be conducted to disentangle individual- and organization-level variance components and test the factorial structure of the SyMOA dimensions across levels of analysis.

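### Internal consistency is scheduled only in the n=150 item-selection stage; estimating it per subscale in the planned n=800 would be a free improvement

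*Protocol article*

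**What the plan says.** - **Sample.** In the Protocol article, section Power, the 150 respondents are "used for the iterative development of the questionnaire to check the retest reliability, internal consistency, and item analyses". The support for 150 is a cited rule that such statistics "require between 100 and 200 people for a robust estimate". No target coefficient or precision is given.
- **Time point.** In Table 2 (Study Procedure and Measures), "Internal consistency of the scale" stands in the T1 to Tx block. The Tx+2 block, for the sample of 800, has "Factorial validity of the scales" together with sociodemographic, discriminant and external-criterion measures. It has no reliability row.
- **Selection in the same stage.** Items are revised on their performance in the n=150 panel data, with a discriminatory power cut-off of 0.3 (Statistical Analysis). The stopping rule is: "The development process will be completed if no further adjustment of the items is necessary".
- **Timing.** The Abstract says that panel data collection "concluded in late August 2025, with iterative item analysis conducted thereafter".
- **Level.** Table 2 uses the singular, scale. Statistical Analysis uses the plural, scales, and names no sample. Future Directions says that "scoring is conceptualized at the level of factor scores for the subscales of dimension 1".

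**The concern.** Reliability is one of the two properties the study sets out to determine. The one place where Table 2 schedules internal consistency is the stage in which items are kept or changed according to how well they correlate with the rest of the scale. Alpha is driven by those same correlations. An item whose correlation is high by chance tends to be kept, one whose correlation is low by chance tends to be changed or dropped, and alpha on the survivors inherits the luck. A later sample of 800 that answers the final questionnaire carries no such selection and gives a narrower interval, yet Table 2 does not use it for this purpose. What is at stake is the internal-consistency figure that readers will take as the instrument's reliability.

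**Working it through.** **The plan's own figure.** The 150 cannot be reproduced from a formula, because it is taken from a cited range. It does lie inside the stated 100 to 200.

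**Inputs from the protocol:** n=150 for development; n=800 at Tx+2; 158 draft items; 5-point responses; discriminatory power above 0.3; planning communality above 0.50 (Power, for the confirmatory factor analysis). 
**Assumed, because not stated for dimension 1:** 8 subscales of about 20 items, the range of loadings, and the final subscale length.

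**Step 1: optimism from selecting and estimating in the same data.** Five-point items were simulated. Items were kept on corrected item-total correlation in n=150, and alpha of the kept items in that sample was compared with alpha of the same items in a new n=800. Mean differences (selecting sample minus new sample), per subscale:

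| Assumed loadings | Only the 0.3 rule | Cut from 20 to 10 items | Cut from 20 to 5 items |
|---|---|---|---|
| 0.2 to 0.6 | +0.03 | +0.036 | +0.07 |
| 0.3 to 0.7 | +0.006 | +0.016 | +0.04 |
| 0.5 to 0.8 | 0.00 | +0.008 | +0.02 |

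For loadings of 0.2 to 0.6 under the 0.3 rule, for example, alpha was 0.761 in the selecting sample and 0.732 in the new one: 0.761 − 0.732 = 0.029. Two variants with stepwise removal and 3000 new cases gave 0.790 − 0.768 = 0.022 and +0.035 for 20 candidate items, hence the range 0.02 to 0.035. With weaker items (loadings 0.1 to 0.5) the excess was 0.785 − 0.740 = 0.045 for 40 candidates and 0.655 − 0.564 = 0.091 for 20 candidates with stepwise removal, and about 0.13 for a subscale in the main set-up.

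**Step 2: the protocol's planning value.** If each item loads on one factor, a communality of 0.50 means a loading of √0.50 = 0.71. With loadings of 0.71 to 0.85 the excess was 0.000 for 10, 20 and 40 candidate items.

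**Step 3: a fresh 150 in every round, stopping when no item fails.** The excess was +0.015, +0.009 and 0.00 for loadings 0.2 to 0.6, 0.3 to 0.7 and 0.5 to 0.8.

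**Step 4: precision.** Feldt 95% interval: 1 − (1 − α)·F, with F the 0.975 and 0.025 quantiles on n − 1 and (n − 1)(k − 1) degrees of freedom. Take α = 0.70 and k = 8 (assumed).
- n=150: F = 1.261 and 0.775. 1 − 0.30 × 1.261 = 0.62; 1 − 0.30 × 0.775 = 0.77.
- n=800: F = 1.108 and 0.899. 1 − 0.30 × 1.108 = 0.67; 1 − 0.30 × 0.899 = 0.73.

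The width falls from about 0.15 to about 0.06, whatever the bias.

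**Step 5: why the level must be named.** Alpha from k items with mean inter-item correlation r is kr / (1 + (k − 1)r). With r = 0.10, 10 items give 1.0/1.9 = 0.53 and 80 items give 8.0/8.9 = 0.90. The same item quality reads very differently at subscale and at pool level. (80 is the protocol's minimum for the preliminary pool, not a stated final length.)

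**The case against.** Four points count against a stronger reading.

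- **Bias is not established.** A reader might infer that the reported reliability is bound to be inflated. The protocol plans on communalities above 0.50, and at that value the excess is nil. The weak-item cases describe a pool that the protocol does not assume, and it states no hard cut to a few items per subscale. This stands. Only the conditional claim, that the coefficient can be optimistic, is supported.
- **Reuse of the same answers is an inference.** The Abstract's timing fits it. But the protocol also speaks of several rounds and limits each person to one or two completions, and a reworded item cannot be checked on old answers. This stands too. Fresh rounds would leave at most about 0.015 for assumed loadings of 0.2 or higher.
- **A single overall alpha is not planned.** A reader might infer one from Table 2. That rests on one singular noun, against the plural in Statistical Analysis and subscale scoring in Future Directions. It is inconsistent wording and no more.
- **The n=800 is not excluded.** Statistical Analysis names no sample for internal consistency, and the factor analysis will check loadings there against 0.4. That is true, but it does not answer the point. The two places that do assign a sample or time point both name development, and a loading check is not a reported reliability estimate.

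It can also be said that internal consistency has no acceptance threshold, so no decision turns on it. That lowers the urgency; it gives no reason to report the estimate from the weaker sample.

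**Conclusion.** The point holds in a limited form. The Power section and Table 2 place internal consistency in the stage that also selects the items, and nothing is scheduled at Tx+2. The development value can be too high by about 0 with good items or at the planned communalities, by about 0.02 to 0.035 for a 20-item subscale with loadings of 0.2 to 0.6, and by more with weaker items or hard cuts. These sizes rest on assumed loadings, number of subscales and final length. The gain in precision at n=800 does not depend on the loadings, although the interval shown assumes alpha 0.70 and 8 items. The comparison treats the 800 as respondents who did not take part in item selection. This is a free improvement, not an error that undermines the study.

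**What to change.** - In Table 2, add internal consistency to the Tx+2 block: per subscale, for the final items, in the n=800, with a 95% confidence interval. State that this is the study's reliability result.
- In the Power section and the T1 to Tx block, describe the n=150 coefficients as development values.
- Use subscales consistently in Table 2, Statistical Analysis and Future Directions.

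The data are already planned, so the cost is a few words and minutes of analysis. The one downside is that the reported figure may be slightly lower.

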#### Statistical Analysis

The quantitative data will be analyzed using SPSS (IBM Corp), R (R Foundation for Statistical Computing), and JASP. The following statistical evaluations will be performed: a CFA (global fit using the chi-square test and goodness-of-fit indexes [root mean square error of approximation<0.05; Tucker-Lewis index and comparative fit index>0.9]), local fit (factor loadings>0.4), iterative item analyses (item distribution and variance, item difficulty [0.2-0.8], and discriminatory power [>0.3]), and verification of correlations and internal consistency of the scales (retest reliability [>0.7] and discriminant validity). The data from the confirmatory sample will also be checked for correlations between variables.

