## Results

As of April 2025, a first draft of 158 items has been developed based on dimension 1 of the SyMOA framework. These items cover constructs such as organizational self-regulation, perception of challenges, modes of communication, and attachment capacity. The draft has undergone an expert review process with 2 OPD-trained experts, who provided feedback on content validity and conceptual alignment. On the basis of this feedback, approximately 20% of the items have been revised to enhance clarity and theoretical precision.

Data collection using the online panel is scheduled for the end of May 2025. Iterative item analyses, including evaluation of item distributions, reliability, and preliminary factor structure, will be conducted following data collection.

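### Cutoffs applied to a single CFA model do not show that the dimension 1 subscales are distinct, and an uncorrected chi-square cannot serve as pass/fail for a long form

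*Protocol article*

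**What the plan says.** All references are to the protocol article.

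- **Statistical Analysis** gives the CFA criteria: "global fit using the chi-square test and goodness-of-fit indexes [root mean square error of approximation<0.05; Tucker-Lewis index and comparative fit index>0.9", with a local criterion of loadings above 0.4. It states no significance level, no estimator and no rule for combining the chi-square result with the indexes.
- **Study Procedure and Measures** says that the CFA tests the structure derived from the SyMOA construct. No competing model is named. On the item pool it says: "The aim is to have at least 80 items, which will be answered on a 5-point Likert scale". The items are then to be "refined iteratively based on their psychometric performance", so the length of the form that reaches the CFA is not fixed.
- **Results** reports that "a first draft of 158 items has been developed based on dimension 1".
- **Power** says that "the aim is to achieve a sample size of at least 800", from a cited rule of thumb that assumes communalities above 0.50 and about 20 factors over all three dimensions. The number of factors for dimension 1 alone is not given.
- **Future Directions** says that "scoring is conceptualized at the level of factor scores for the subscales of dimension 1", and leaves higher-order structures to later research.

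**The concern.** Subscale scores need evidence that communication, attachment, awareness and regulation can be told apart. Adequate fit of one multi-factor model is not that evidence. If the factors may correlate (the article does not say), a one-factor structure is the special case in which all factor correlations equal 1. Data with a single general factor would therefore fit the subscale model well and satisfy the index cutoffs. The question is whether anything else in the stated criteria would expose this.

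Two things could: the cutoffs might be strict enough to exclude a one-factor model, or the chi-square test might arbitrate. If neither does so reliably, the study could report subscales as confirmed when they are close to one dimension. If chi-square is binding on a long form, it could instead reject a structure that is correct. Because the article does not say how chi-square counts, that choice could be made after the data are seen.

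**Working it through.** **The plan's own figure.** The sample size of 800 comes from a cited rule of thumb whose formula is not in the article, so it cannot be reproduced. It is taken as given.

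**Inputs.** From the article: N = 800; a pool of at least 80 items, currently 158; communality 0.50, so loading √0.50 ≈ 0.71; the stated cutoffs. Assumed: four equal-sized factors (Research Objectives names four capacities as examples), normal-theory maximum likelihood, a 5% test level, and a range of factor correlations φ, since the article gives none.

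**Step 1: chi-square under a correct model.** With p items, the uncorrected statistic is inflated by roughly 1/c, where c = 1 − (2p + 11)/(6N). The rejection rate is then about P(χ²(df) > c × χ²(df; 0.95)), with df = p(p+1)/2 − 2p − 6.

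For p = 80: df = 3240 − 160 − 6 = 3074; c = 1 − 171/4800 = 0.964; the critical value is 3204.1; 0.964375 × 3204.1 = 3090.0; the rejection rate is 0.416.

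| Items | df | c | Approximation | Simulation, correct model |
|---|---|---|---|---|
| 40 | 734 | 0.981 | 10% | 8% |
| 60 | 1704 | 0.973 | 20% | 20% |
| 80 | 3074 | 0.964 | 42% | 40–41% |
| 158 | 12239 | 0.932 | 100% | 100% |

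The simulations used normal data, loading 0.71 and factor correlation 0.5. With 20 factors the 80-item rate was 48%. With 5-point responses treated as continuous it was 70%. A Swain correction brought the 80-item rate from 39.7% to 5.0% (300 runs) and the 60-item rate from 20.5% to 6.5% (200 runs), so model size is the cause in normal data.

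**Step 2: a one-factor model fitted to four true factors.** With equal loadings λ and m = p/4 items per factor, the population fit has a closed form. The covariance matrix has these eigenvalues:

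- e0 = 1 − λ² (p − 4 times)
- e1 = e0 + mλ²(1 − φ) (3 times)
- e2 = e1 + pλ²φ (once)

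The one-factor fit reproduces the mean correlation r = [(m−1)λ² + (p−m)λ²φ]/(p−1). Its misfit is F1 = (p−1)ln(1−r) + ln(1+(p−1)r) − ln|Σ|. The baseline misfit is F0 = −ln|Σ|.

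For p = 80, λ = 0.71, φ = 0.85:

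- e0 = 0.4959, e1 = 2.0082, e2 = 36.287, so ln|Σ| = −47.622
- r = 0.4467, so the fitted loading is √0.4467 = 0.67
- F1 = −43.161 + 47.622 = 4.461, with df 3080; F0 = 47.622, with df 3160
- RMSEA = √(4.461/3080) = 0.038
- CFI = 1 − 4.461/47.622 = 0.906
- TLI = 1 − (4.461/3080)/(47.622/3160) = 0.904

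| Items | Loading | φ | RMSEA | CFI | TLI | Fitted loading | Numeric cutoffs |
|---|---|---|---|---|---|---|---|
| 80 | 0.71 | 0.70 | 0.059 | 0.770 | 0.764 | 0.62 | fails |
| 80 | 0.71 | 0.80 | 0.046 | 0.862 | 0.859 | 0.65 | fails |
| 80 | 0.71 | 0.85 | 0.038 | 0.906 | 0.904 | 0.67 | passes |
| 80 | 0.71 | 0.90 | 0.029 | 0.947 | 0.946 | 0.68 | passes |
| 80 | 0.50 | 0.70 | 0.028 | 0.851 | 0.847 | 0.44 | fails |
| 80 | 0.50 | 0.80 | 0.021 | 0.921 | 0.919 | 0.46 | passes |
| 158 | 0.71 | 0.85 | 0.030 | 0.887 | 0.886 | 0.67 | fails |
| 158 | 0.71 | 0.90 | 0.024 | 0.933 | 0.932 | 0.68 | passes |
| 40 | 0.71 | 0.85 | 0.046 | 0.929 | 0.925 | 0.67 | passes |

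In simulated samples of 800 (80 items, loading 0.71, 40 runs each), the one-factor fit met all numeric cutoffs in 72% of runs at φ = 0.85 and 100% at φ = 0.90. The uncorrected chi-square rejected it in every run.

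**Step 3: does a direct comparison help?** In the simulated scenarios the one-factor and four-factor chi-squares differed by about 1,280 to 3,550 on 6 df. The BIC penalty for 6 parameters is 6 × ln 800 ≈ 40, so BIC would choose four factors decisively even at φ = 0.90. A fit comparison alone therefore separates factors that are nearly collinear, and a bound on the correlations is needed as well.

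**The case against.** The strongest reply is that chi-square belongs to the stated criteria and rejected the one-factor model every time. A reader might infer that a one-factor model can pass everything the plan states. It cannot if chi-square is binding. What stands against the reply is that, on a long form, the same test also rejects the correct model: 70% of the time with 80 five-point items and always with 158. There it does not tell right from wrong, and the article does not say whether it is binding.

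Second, the item count is open. The 80 items are an aim for the preliminary pool and the 158 are a draft, so a short form may reach the CFA. This is a fair limit on the chi-square half: at 40 items the excess rejection is small. It does not rescue the indexes, because the one-factor model still passes at 40 items with φ = 0.85.

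Third, the one-factor model passes only with highly correlated factors. Also true. A reader might infer that the cutoffs can never support subscales. They do exclude one factor at correlations of 0.70 or lower, and at 0.80 with 80 items and loadings of 0.71.

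Fourth, the cutoffs are conventional, and an article may leave estimator and model comparisons to a fuller document. Their absence alone would be no finding. But this article does fix one model, absolute cutoffs and subscale scoring, and it defers higher-order structures. The planned check of correlations between variables is not tied to any decision on subscale distinctness.

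A reader might also suspect that the item wording ("mostly formulated negatively, with 20% formulated positively") creates an artificial factor. The article gives nothing from which to size that, so it forms no part of this point.

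**Conclusion.** The point holds in a limited form: the stated fit criteria, applied to one model, do not by themselves show that the dimension 1 subscales are distinct.

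- **Numeric cutoffs alone, chi-square set aside.** They accept a one-factor model when true factors correlate about 0.85 or more, or about 0.80 with loadings near 0.5. With 158 items and loadings of 0.71 the threshold lies between 0.85 and 0.90. This rests on four equal factors with equal loadings. Whether the real correlations are that high is unknown. It is plausible, since one respondent rates one organization on related capacities.
- **Chi-square.** For a form of 80 to 158 items at n=800, the uncorrected statistic rejects a correct model about 40% to 100% of the time, falling to about 20% at 60 items and 8% to 10% at 40. This assumes maximum likelihood and a 5% level, neither of which the article states.

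The documents do not support saying that the criteria can never establish subscales, or that a one-factor model satisfies every listed criterion including chi-square. The change is worth making because the planned subscale scores depend on this result.

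**What to change.** For the n=800 CFA, state in advance:

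1. A one-factor model is fitted as a competitor to the correlated-subscale model. A second-order model is optional.
2. Subscales are reported as separate only if the correlated model fits better (for example by BIC and the CFI difference) and the upper 95% limit of each factor correlation lies below a bound fixed beforehand, for example 0.90. Subscales that miss the bound are merged.
3. The estimator suits 5-point items (categorical or robust).
4. Chi-square is reported descriptively with a model-size correction such as Swain's, and is not used as a pass/fail test.

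The cost is a few extra model fits on data already planned, with no additional participants. The downside is that some subscales may have to be merged.

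### The item limits that bear on subscale membership test each item only against its own subscale, so with correlated subscales a small share of mis-keyed items can pass them and RMSEA, CFI and TLI

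*Protocol article*

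**What the plan says.** All numeric limits stand in the Statistical Analysis section of the protocol article.

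- Item level, first in the confirmatory factor analysis (CFA) and then in the item analysis: "local fit (factor loadings>0.4), iterative item analyses (item distribution and variance, item difficulty [0.2-0.8], and discriminatory power [>0.3". Distribution and variance carry no cut-off.
- Global fit: "global fit using the chi-square test and goodness-of-fit indexes [root mean square error of approximation<0.05; Tucker-Lewis index and comparative fit index>0.9". The chi-square test has neither a significance level nor a decision rule.

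The section on study procedure gives the CFA the task of checking the theoretical factor structure. Discriminant validity is set there, and in Table 2, against an external questionnaire on the respondent's own personality structure, not against the other subscales of the new instrument. Future Directions fixes the output: "In this study, scoring is conceptualized at the level of factor scores for the subscales of dimension 1". Phase 2 structural or factor analyses and a check of correlations between variables in the confirmatory sample are also planned, without a criterion.

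**The concern.** An item that truly measures a neighbouring subscale still correlates with the subscale to which it is wrongly keyed, by roughly its loading times the correlation between the two factors. With correlated subscales that product can exceed 0.3 and 0.4. Neither limit asks whether the item relates more closely to another subscale.

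The label matters too. A loading is a parameter estimate. Local misfit shows in the differences between observed and model-implied correlations, which the stated definition of local fit does not use.

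Results are scored per subscale, so misplaced items contaminate those scores and push the subscales together. In the case of 8 mis-keyed items of 80 worked below (loading 0.6), an estimated factor correlation rises from a true 0.70 to 0.75. The study could then report the theoretical item assignment as locally confirmed on evidence that does not test it.

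**Working it through.** **Inputs from the article.** Loading >0.4; discriminatory power >0.3; RMSEA <0.05; CFI and TLI >0.9; CFA sample 800; communality above 0.50; at least 80 items planned; 150 respondents in phase 2.

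**Assumed, because the article does not give them.** Factor correlation φ (0.3 to 0.9); number of subscales (4 in the cases shown; the article names four constructs as examples); true loading λ (0.6, or 0.707 = √0.50 from the stated communality); number of mis-keyed items; alpha 0.05 for chi-square.

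**The plan's own figure.** "the aim is to achieve a sample size of at least 800 following the rule of thumb by Bühner", with "approximately 20 factors across all dimensions". The formula of the rule is not in the article, so 800 cannot be reproduced (it equals 800/20 = 40 per factor, or 800/80 = 10 per item). The point does not depend on it. The communality does matter: 0.50 means λ = 0.707, while a loading of 0.4 is a communality of only 0.4² = 0.16. That distance is the room a foreign item has.

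**Closed form, one foreign item among m own items.**

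- Item-rest correlation with the wrong subscale: r = λ²φm / √(m + m(m−1)λ²). With λ² = 0.5 and m = 10: r = 5φ/√55 = 0.674φ. It exceeds 0.3 when φ > 0.445.
- Loading on the wrong factor, approximately λφ. It exceeds 0.4 when φ > 0.4/0.707 = 0.566. In the fitted CFA, where the item itself helps to define the factor, the limit is passed from φ of about 0.52 (loading 0.402).
- With λ = 0.6 the fitted loading is 0.380 at φ = 0.55 and 0.413 at φ = 0.6.

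**Maximum-likelihood CFA fitted to the population correlation matrix with the wrong keying.**

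| Layout, λ | φ | Mis-keyed | Item-rest r: keyed / true | Loading | RMSEA | CFI | TLI | Numeric limits |
|---|---|---|---|---|---|---|---|---|
| 4×10, 0.707 | 0.3 | 1/40 | 0.20 / – | 0.23 | – | – | – | caught by both item limits |
| 4×20, 0.6 | 0.5 | 8/80 | – | 0.338 | – | – | – | caught by the loading |
| 4×20, 0.6 | 0.6 | 8/80 | 0.36 / – | 0.403 | – | 0.927 | – | just passes |
| 4×20, 0.6 | 0.7 | 8/80 | 0.42 / 0.57 | 0.465 | 0.022 | 0.946 | 0.944 | passes |
| 4×20, 0.707 | 0.6 | 8/80 | 0.44 / 0.69 | 0.457 | 0.033 | 0.923 | 0.921 | passes |
| 4×10, 0.707 | 0.6 | 4/40 | – | 0.468 | 0.046 | 0.921 | 0.916 | passes |
| 4×20, 0.707 | 0.6 | 16/80 | 0.48 / 0.69 | 0.487 | 0.046 | 0.853 | 0.849 | fails CFI and TLI |
| 4×10, 0.707 | 0.6 | 8/40 | – | – | 0.063 | 0.851 | – | fails |

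A dash marks a value not needed for the conclusion.

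**Chi-square, fourth row.** df = 80×81/2 − (80 + 80 + 6) = 3240 − 166 = 3074. Expected value = 3074 + 799 × 3074 × 0.022² ≈ 4263, against a critical value of about 3204. Power is about 1.00. With a single mis-keyed item of 40 it falls at high φ: for λ = 0.707, 0.86 at φ = 0.85 and 0.50 at φ = 0.9; for λ = 0.6, 0.59 at φ = 0.8.

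**What would expose the item.** In the fourth row, the true correlation of a mis-keyed item with an item of its real subscale is 0.6² = 0.36. The model implies about 0.465 × 0.75 × 0.6 = 0.209. The residual is about 0.15, and it repeats across the items of the real subscale. Over the settings run, such residuals were about 0.10 to 0.29.

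**The case against.** Four stronger readings are tempting, and the article does not support them.

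- *Every stated check passes.* It does not. Chi-square is listed first under global fit and rejects at N=800 in all the 10% settings. What remains is that it has no decision rule, also rejects for trivial misfit at that size, and does not point to an item.
- *These are the only item rules.* Difficulty, distribution and variance are also listed, though they say nothing about assignment.
- *Mis-keyed items pass in general.* Only if φ is high enough and the mis-keyed items are few. At φ = 0.3 a single one fails both limits; at φ = 0.6 about 20% mis-keyed fail CFI and TLI. At λ = 0.6 and φ = 0.6 the loading of 0.403 is so close to the limit that sampling error would put many such items below it. Nothing in the article suggests that 10% of the items are in fact misplaced.
- *No cross-loading rule exists.* The planned factor analyses and correlation checks are where cross-loading could be seen, and a condensed article may leave their criteria to a fuller document. A missing rule is therefore not the finding.

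The case against λ = 0.6 as too low for a plan that assumes communality above 0.50 does not help the plan: at 0.707 mis-keyed items pass from a lower φ. Nor is the matter only one of labelling, because the article itself fixes what counts as local fit, and that definition does not test assignment.

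**Conclusion.** The stated numeric limits do not test whether an item sits on the right subscale. With subscales correlated at about 0.55 to 0.6 or more, up to roughly 10% mis-keyed items pass discriminatory power, loading, RMSEA, CFI and TLI together; chi-square would signal misfit without locating it.

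The size rests on an assumed factor correlation, equal loadings, a four-subscale layout in the cases shown and population values without sampling error. Correlations in that range are plausible, since communication, attachment, awareness and regulation are facets of one internal level of functioning rated by one respondent, and the article foresees higher-order factors. If the subscales turn out to correlate clearly below 0.5, the existing limits largely suffice. This is a correctable weakness in how local fit is defined, not a flaw in the design.

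**What to change.** - **Phase 2** ("A sample size of 150 will be used for the iterative development of the questionnaire"): for each item, compare its corrected correlation with its own subscale with its correlation with every other dimension 1 subscale. Flag for review, not for automatic removal, any item whose own correlation is not the largest. Do not require a minimum gap such as 0.10: in simulation at n=150 with loading 0.6 and 4×20 items, that would flag about 25% (φ = 0.7) to 65% (φ = 0.8) of correctly keyed items, against 0.3 to 3% for the plain comparison. False flags become more frequent with more and shorter subscales, which is a further reason to review rather than delete. The Abstract reports the panel collection as complete, so the check can be run on data in hand.
- **Phase 4:** keep loading >0.4, and define local fit also by standardized residual correlations (about |r| >0.10, read as a pattern across an item's residuals, not as single pairs) and by modification indices for cross-loadings. Report any item reassigned on this basis as exploratory.

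The cost is a few lines of R, a sentence in Statistical Analysis, and some items reviewed or moved.
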